#### Analyses for Aims 1–3: Evaluation of HOPS vs. TAU/WL and comparison of HOPS-ST to HOPS-RT.

*Hypothesis 1:* Students in HOPS-ST will demonstrate significantly fewer OTMP skills deficits and homework problems and will show significantly better academic performance at post-treatment compared to students in TAU-WL*Hypothesis 2:* Students in HOPS-RT will demonstrate significantly fewer OTMP skills deficits and homework problems and will show significantly better academic performance at post-treatment compared to students in TAU-WL.*Exploratory:* Examine whether the effects of HOPS-ST and HOPS-RT differ at post-treatment and follow-up.

A linear mixed-effects modeling approach will be used to examine intervention effects at post-treatment. An intent-to-treat approach to data analysis will be applied, including all children with baseline data in the analytic model. Under this approach, we will examine differences between students in HOPS (for HOPS-ST and HOPS-RT separately) vs. TAU-WL (as well as for students in HOPS-ST vs. HOPS-RT) by fitting a multilevel model in which students are nested within schools. In addition to including an indicator variable for the treatment condition, we will include covariates that explain variation at the student and school levels. To explore the sustainability of the intervention effect, we will examine how both means and slopes (rates of change) vary from baseline to 6-month and 12-month follow-up using regression analyses. Changes in mean and slope reflect variations in the magnitude of effect and pace of change during different phases of the study.

Because the efficacy of HOPS will be evaluated on three different domains of outcome measures (organizational skills, homework performance, academic achievement), we will use a Bonferroni-adjusted significance level to correct for multiple comparisons within each domain. As a result, the significance level will be adjusted to.025 per domain for the two measures of organizational skills (COSS-P, COSS-T), the two measures of homework performance (HPC, HPQ-T), and the two measures of academic achievement (APS, academic grades).

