Power calculations were based on the following design parameters: *N = 30* schools (20 assigned to HOPS, 10 assigned to TAU); ICC = 0.04 (based on [4]); α=0.025  (reflecting the Bonferroni corrected significance level to accommodate multiple testing of two outcomes for each outcome domain); and $R^{\text{2}}=\text{0}.\text{6}\text{0}$ at the student and school level (which is the proportion of variation in outcomes explained by student and school-level covariates). Based on initial projections, we expected to enroll 8 students per school for a total of 240 participants (216 with 15% attrition), which would be sufficient to identify a minimal detectable effect size (MDES) of 0.41. Because of recruitment challenges primarily due to barriers related to the COVID-19 pandemic, we adjusted these projections to an average of 4.5 students/school for 30 schools for a total of 135 participants (122 with attrition). This sample size will result in a MDES of 0.48 with adequate power (80%). Based on prior research by [name] and colleagues [4], the MDES for primary outcomes in our study is well within the range of expected effect sizes.

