#### Analyses for Aim 5: Effect modification.

Our plan is to explore the moderating effect of severity of organization problems, ADHD, oppositional defiant behavior, and internalizing symptoms, ADHD medication status, as well as socioeconomic level (i.e., caregiver level of education, Area Deprivation Index) at baseline on the effectiveness of HOPS. These moderators will first be examined individually in the previously described mixed effects models. Baseline scores on the moderators that are continuous variables will be centered in relation to the group-mean within each school. The moderators will be examined as a moderator by treatment group interaction term in each of the multi-level models. Significant interaction effects for both continuous and discrete variables imply moderation effects, where the magnitude and sign of the estimated coefficients reflect the moderated change in treatment effect. Following the analytic plan used by [name] and colleagues [4], significant interaction effects among the continuous moderators will be examined at the 25^th^, 50^th^, and 75^th^ percentile levels of the moderator. For the discrete variable (medication status), we will compare treatment effects for students on and off medication at baseline to assess the magnitude of the moderating effects. In addition, we will examine the combined effect of multiple moderators. This will be done by incorporating multiple interaction terms and several higher order interaction effects in the mixed effects models (see analytic plan for Aims 1–3). The purpose of these analyses is to explore whether the inclusion and exclusion of specific moderator variables augment or attenuate the moderating effect of different variables.

Similar to [name] and colleagues [4], we will formally test the significance of moderator effects using the models described for Aims 1–3. We will also examine the proportion of variation in the outcomes that is explained by the moderators, given by the magnitude of the adjusted R^2^ values. In addition, we will report the 95% confidence intervals for the moderator by treatment group interaction, because confidence intervals provide more precise information about the magnitude of the moderator effect [42].

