#### Analyses for Aim 6: Association of fidelity, engagement, working alliance to outcomes.

Our plan is to evaluate the extent to which provider intervention fidelity, student and caregiver engagement, and provider-student working alliance are associated with outcomes for participants in HOPS using multiple linear regression models. We will determine the proportion of variance in the outcome that is explained by the implementation factors, as assessed using adjusted R^2^ measures. Additionally, we will formally test the significance of the estimated coefficients to identify which implementation factor(s) are predictive of changes in the outcome measures.

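### Aim 5 reads the variation explained by the moderators from an adjusted R² that also contains the covariates' share; it should be the increment due to the moderator-by-treatment terms

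*Protocol article*

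**What the plan says.** All references are to the Protocol article.

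- **Aim 5 section, model.** "These moderators will first be examined individually in the previously described mixed effects models". Each moderator enters with a moderator-by-treatment interaction. Models with several moderators together are also planned.
- **Aim 5 section, summary measure.** The plan will examine the "proportion of variation in the outcomes that is explained by the moderators, given by the magnitude of the adjusted R^2^ values".
- **Aims 1–3 section, model.** Students are nested within schools. Besides the treatment indicator, "we will include covariates that explain variation at the student and school levels".
- **Aims 1–3 section, power paragraph.** R² is set at 0.60 at student and school level, "which is the proportion of variation in outcomes explained by student and school-level covariates".
- **Aim 6 section.** Fidelity, engagement and working alliance are related to outcomes "for participants in HOPS using multiple linear regression models". The summary is the "proportion of variance in the outcome that is explained by the implementation factors, as assessed using adjusted R^2^ measures". No baseline score or other covariate is named for this regression.

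**The concern.** The quantity named in Aim 5 is what the moderators explain. The statistic chosen to measure it describes everything in the fixed part of the model: treatment, covariates, moderator main effects and interactions together. The plan itself assumes that the covariates are strongly predictive, so most of the reported figure would belong to them.

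Two features add to the problem.

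- Several moderators are likely to be prognostic. Baseline severity of organization problems is one of them, and the COSS, which measures organization, is an outcome. Such a variable can predict the outcome well without changing the treatment effect at all. Its main effect is not evidence of moderation.
- The Aims 1–3 models are multilevel. Variance is split between students and schools, and there is more than one way to define R². Adjusted R² as written cannot be computed there without a further choice.

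At stake is a descriptive figure that readers may use to judge who benefits from HOPS, which the Discussion says the study will identify. A moderator set with no effect could be reported as explaining more than half of the variation. A real contribution of a few percent could not be told apart from none.

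**Working it through.** **Inputs**

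- Covariate share of outcome variance: 0.60 (power paragraph). This is a planning assumption, so there is no calculation in the plan to reproduce. Shares of 0.30, 0.40 and 0.50 were also tried.
- Sample: "total of 135 participants (122 with attrition"; 30 schools; ICC 0.04 (power paragraph).
- Number of moderators: one at a time, or all seven listed in the Aim 5 section (organization problems, ADHD, oppositional defiant behavior, internalizing symptoms, medication status, caregiver education, Area Deprivation Index).

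**Formula**

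Adjusted R² = 1 − [RSS/(n − p − 1)] / [TSS/(n − 1)], with p the number of terms in the model.

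Terms that explain nothing lower RSS, on average, only in proportion to the degrees of freedom they use. RSS/(n − p − 1) therefore stays at the residual variance. With total variance set to 1:

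- Covariates explain 0.60, moderators nothing: 1 − 0.40/1 = 0.60.
- Covariates explain 0.30, moderators nothing: 1 − 0.70/1 = 0.30.
- Covariates explain 0.60, moderators truly add 0.02: 1 − 0.38/1 = 0.62, while the increment is 0.62 − 0.60 = 0.02.

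**Simulation for Aim 5**

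The data had n = 122 in 30 schools, ICC 0.04, and moderators with neither a main effect nor an interaction. Fits were by least squares, with 3,000 to 4,000 replicates. The reduced model held covariates and treatment; the full model added the moderators and their interactions.

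| Covariate share | Moderators | Reduced model, mean adjusted R² | Full model, mean adjusted R² | Increment |
|---|---|---|---|---|
| 0.60 | 1 | 0.596 | 0.596 | 0.000 |
| 0.60 | 7 | 0.597 | 0.598 | 0.000 |
| 0.50 | 1 | 0.496 | 0.495 | 0.000 |
| 0.40 | 1 | 0.398 | 0.398 | 0.000 |
| 0.30 | 1 | 0.298 | 0.298 | 0.000 |

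With one moderator and a covariate share of 0.60, the 5th to 95th percentile range of the full-model figure is 0.50 to 0.69. Sampling variation alone is thus far larger than a contribution of 0.02. Because the fits are by least squares, they show how adjusted R² behaves; they do not stand in for any particular mixed-model R².

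**Same check for Aim 6**

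Five implementation factors with no effect were used, with n = 81 (two thirds of 122) and n = 90 (two thirds of 135).

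- Only the factors in the regression: mean adjusted R² 0.000, for the post-treatment score and for the change score.
- Baseline score added, post-treatment score as outcome, baseline share 0.60: mean adjusted R² 0.594 to 0.595, increment 0.000.

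The Aim 6 figure is therefore correct or misleading depending on a term that the section does not mention.

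**The case against.** The strongest reply is that the Aim 5 sentence is condensed and names the right target. It speaks of adjusted R² values in the plural, and the preceding paragraph already plans models that include and exclude particular moderators. A difference between models may be intended, and the choice between partial, marginal or incremental R² is often left to a statistical analysis plan. This stands only in part. The text takes the magnitude of the values, not a change in them, and names no reference model. The remark on inclusion and exclusion concerns how moderating effects strengthen or weaken one another. The rule as printed gives the wrong figure, whatever was intended.

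The reply is right that the consequence is limited. Aim 5 is exploratory and R² is one summary among several. The plan also gives interaction tests, treatment effects at three percentiles of each continuous moderator, and 95% confidence intervals for the interactions. None of these depends on how R² is defined, and a moderator with no effect would be shown beside an interval centred near zero.

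A reader might also infer three stronger things that the document does not support.

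- **That Aim 6 has the same error.** Its section names only the implementation factors and does not refer back to the Aims 1–3 covariates. Its stated aim to "identify which implementation factor(s) are predictive of changes in the outcome measures" does not force a baseline term, because a change score can be the outcome.
- **That about 60% will be reported.** The 0.60 is a power input; the reported figure would follow whatever the covariates really explain.
- **That the baseline score is certainly in the Aim 5 models.** The Aims 1–3 section speaks of covariates without naming it. The point needs only that predictive covariates are present, which the section does say.

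**Conclusion.** The point holds for Aim 5. Read as written, the variation credited to the moderators would be roughly the share explained by the covariates: about 0.60 at the planning value and about 0.30 to 0.50 at the lower shares tried, when the true contribution is zero. This assumes that the adjusted R² is that of the whole model and that covariates enter as the Aims 1–3 section says. The size depends on their actual predictive strength; the direction does not.

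For Aim 6 no error is shown. Adjusted R² is the right quantity for a regression that holds only the implementation factors, and it would mislead only if a baseline score or other covariates were added.

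The severity is low. No hypothesis test, confidence interval or sample size is touched.

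**What to change.** **Aim 5.** Fit each model twice, with and without the moderator-by-treatment terms, keeping the moderator main effects, treatment and covariates in both. Report the change in marginal R², or the proportional reduction in student- and school-level residual variance, and say which is used. Keeping the main effects in both fits stops prognostic value from being counted as moderation.

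**Aim 6.** State which terms are in the regression. If only the implementation factors are included, keep adjusted R². If a baseline score or other covariates are added, report the change in adjusted R² when the factors enter.

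**Cost.** One extra model fit per analysis and a change of wording. The reported percentages will be much smaller than a whole-model figure.

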#### Analyses for Aim 6: Association of fidelity, engagement, working alliance to outcomes.

Our plan is to evaluate the extent to which provider intervention fidelity, student and caregiver engagement, and provider-student working alliance are associated with outcomes for participants in HOPS using multiple linear regression models. We will determine the proportion of variance in the outcome that is explained by the implementation factors, as assessed using adjusted R^2^ measures. Additionally, we will formally test the significance of the estimated coefficients to identify which implementation factor(s) are predictive of changes in the outcome measures.

#### Analyses for Aim 7: Estimate of cost.

We will estimate the incremental cost of HOPS relative to TAU. Cost estimates will differentiate the cost of materials used for training and interventions and costs associated with time spent for training, technical support, and intervention implementation.

## Discussion

The main purpose of the study is to evaluate the effectiveness of the HOPS intervention when provided under authentic practice conditions by professionals working in the schools attended by enrolled students. School providers will receive training and technical support that is commonly offered when attempting to implement an evidence-based program in their schools, in contrast to more intensive consultation and coaching that is often provided through research trials (see [8]). In addition, the study will examine the effectiveness of HOPS when provided in schools by a limited number of study team members who work across multiple schools, which is similar to how the prior large-scale RCT of HOPS was conducted [4]. The study design will enable our team to explore differences in the effectiveness of HOPS when offered by school and research team members and variations in effectiveness related to differences in intervention content and process fidelity, student-provider working alliance, and student and caregiver engagement, as well as the cost associated with intervention implementation.

Strengths of the study include the in-depth monitoring of intervention fidelity by school and research providers, including both content and process fidelity, and the assessment of student and caregiver engagement in the intervention. The assessment of school provider fidelity will provide valuable information about how HOPS is implemented in authentic practice settings, factors contributing to variable implementation, and the association of fidelity to student outcomes. Another strength of the study is the analysis of factors that may contribute to variable effects of intervention, including severity of child symptoms of ADHD, oppositional defiant behavior, internalizing symptoms, as well as family socioeconomic factors, including caregiver level of education and the level of neighborhood disadvantage for participating families (i.e., Area Deprivation Index). Additional strengths of the study are the examination of variables that might account for the impact of HOPS on child academic outcomes and the analysis of the costs of implementing the program in authentic school settings.

All students and families will be enrolled after the height of the COVID-19 pandemic when almost all schools are offering in-person instruction to students. A practical challenge is that schools will continue to experience substantial resource limitations during the period of enrollment. In the early years of the project, personnel in many schools expressed strong interest in the study but limited capacity to support research activities (e.g., implement HOPS, recruit students, contact families for initial consent, and support data collection). To be responsive to this feedback, our study team adapted by changing the research design so that only 50% of enrolled students in the HOPS condition will receive intervention from school providers (with the remaining students getting HOPS from a research provider).

A second practical challenge is that school providers often experience difficulty connecting with families to obtain their approval to be contacted by the study team to obtain caregiver consent and child assent. Our team has collaborated with school partners to identify alternative strategies for reaching out to families of referred students to obtain initial consent (e.g., draft letter for principal to send to families; flyer with QR code for families to indicate their interest in the study and share contact information).

An additional challenge is that school providers often encounter difficulties with the video recording of sessions for fidelity coding. In collaboration with school providers, we have adapted by using the video recording function available through virtual meeting platforms and providing in-person support to school providers to ensure the technology works and images of the school provider and student are being captured.

A potential limitation of the study is that each participating school is required to identify a school staff member willing and able to serve in the role of school provider. We anticipate that many schools will not have sufficient resources to assign a school professional to this role. Therefore, the results will be generalizable to schools having the resources to identify a school professional to serve as HOPS interventionist.

We will report study findings in Clinicaltrials.gov within one year following the end of data collection. disseminate research methods and findings to researchers and practitioners in school and clinical psychology, school mental health, child and adolescent psychiatry, and pediatrics through presentations and publications in peer-reviewed journals. A research brief will be disseminated through centers of excellence at the study institution. Further, in collaboration with our institution’s Communications and Public Relations teams, we will disseminate the results and practical implications to families, teachers, intervention providers, and school administrators through press releases and notifications on our institution’s Facebook pages and X (Twitter), Blue Sky, and LinkedIn feeds. No information that could identify a participant will be included in materials disseminated to professional or lay communities.

The findings of this study will reveal the extent to which HOPS is effective under authentic practice conditions and factors that influence the impact of intervention on student outcomes. This study will also evaluate the impact of HOPS on a wide range of students with OTMP difficulties rather than just for students with ADHD. In addition, the study will identify which students are more likely to benefit from HOPS and how the intervention exerts its effect on outcomes. Importantly, the study will reveal how HOPS is implemented under real-world conditions, without intensive supervision and coaching, while identifying factors that are related to intervention implementation. Overall, the findings of this study will advance understanding of how to implement and sustain the use of evidence-based mental health and education practices in school and community settings.

## Abbreviations

ADHD: Attention-deficit/hyperactivity disorder
APS: Academic Proficiency Scale
COSS: Children’s Organizational Skills Scale
HOPS: Homework, Organization, and Planning Skills
HPC: Homework Problem Checklist
HPQ: Homework Performance Questionnaire
ODD: Oppositional Defiant Disorder
OTMP: Organization, Time Management, and Planning
TAU/WL: Treatment-as-usual/waitlist
